## Abstract

**Abstract:**

**Introduction:**

The development of the target trial emulation (TTE) methodology has enhanced the conduct of non-randomised studies. By leveraging readily available routinely collected data, TTEs offer opportunities for complementing randomised controlled trials (RCTs), providing more precise estimates and improving the external validity of RCTs. To explore this potential, we selected a successfully completed RCT as a case study. In the FIRST-line support for Assistance in Breathing in Children (FIRST-ABC) step-up RCT, high flow nasal cannula (HFNC) was found to be non-inferior to continuous positive airway pressure (CPAP) in terms of time to liberation from respiratory support in the paediatric critical care setting. We will emulate the FIRST-ABC step-up trial using routinely collected data from the Paediatric Intensive Care Audit Network (PICANet) database.

**Methods and analysis:**

This is a protocol for a TTE that will use longitudinally collected data from the PICANet database. The study aims to emulate the FIRST-ABC step-up RCT using an observational study design in a frequentist framework. We will benchmark the results against the published trial. The study will apply a new-user design by selecting children admitted to paediatric intensive care units that started HFNC or non-invasive ventilatory support (as a surrogate for CPAP). The eligibility criteria and selected outcomes will reflect those of FIRST-ABC within the constraints of the available routinely collected data. We will use advanced quantitative doubly robust methods to minimise the impact of confounding by indication and allow for heterogeneity according to child characteristics. The analysis will be repeated using a Bayesian approach for follow-up research.

**Ethics and dissemination:**

The research received ethics approval from the London School of Hygiene & Tropical Medicine Research Ethics Committee. This study will expand the findings from the FIRST-ABC step-up RCT, providing additional insight from a large representative sample using real-world data. The frequentist and Bayesian approaches will enable a discussion about the advantages and drawbacks of the two strategies. The results will be disseminated to the research and clinical community and made accessible to the public. In addition, the study results will be used in future research, which aims to supplement RCTs with additional evidence from a TTE.

STRENGTHS AND LIMITATIONS OF THIS STUDYThis study will emulate the FIRST-line support for Assistance in Breathing in Children step-up randomised controlled trial (RCT), applying advanced design strategies and doubly robust methods to mitigate potential bias typically associated with observational studies, both at the design and at the analysis level.By incorporating both frequentist and Bayesian approaches, the study will facilitate a comparative discussion of their respective advantages and limitations.Replicating a successfully completed RCT allows for a robust benchmark to evaluate the concordance between the target trial results and those derived from its emulation using routinely collected data.The study will serve as a case study within the broader context of integrating external evidence from target trial emulations into RCTs, with the potential to reduce sample size, increase precision and improve external generalisability.Eligibility criteria, study treatments and endpoints replication are constrained by the limits imposed by routinely collected data.

## Introduction

### Background

 Nearly 30% of children admitted to paediatric intensive care units (PICUs) have a respiratory diagnosis.^1^ Non-invasive respiratory support (NRS) is a form of treatment which incorporates various non-invasive techniques aimed at improving alveolar ventilation and oxygenation.^2^ The use of NRS in PICU has increased over time, in recognition of the complications associated with endotracheal intubation.^3^ Continuous positive airway pressure (CPAP) is a standard treatment in NRS, but in the past decade high flow nasal cannula (HFNC) therapy has been introduced as an alternative method, which is better tolerated by the patients and easier to handle by the staff.^4^

FIRST-line support for Assistance in Breathing in Children (FIRST-ABC) step-up was a pragmatic randomised controlled trial (RCT) conducted in the UK among 600 acutely ill children aged 0–15 years, who were clinically assessed to require NRS. The RCT found that HFNC was non-inferior to CPAP in time to liberation from respiratory support.^5^

RCTs can provide unbiased estimates of the relative effectiveness and safety of alternative interventions, but practical constraints preclude well-powered head-to-head RCTs of all alternative interventions for all relevant patient groups.^6 7^ A sample size calculated solely on the primary outcome will prove inadequate for important secondary endpoints and subgroup analyses, with potential serious implications such as erroneous identification of differential subgroup effects, which may lead to inappropriate provision or withholding of treatment.^8^ From the patient perspective, it is important to provide relevant answers for secondary endpoints and underrepresented groups, as noted by the patient representatives consulted during the design of FIRST-ABC. In addition, when RCTs encounter too many challenges to successfully be completed, they are terminated without adequately answering any of their research questions.^9^

In these settings, RCTs may benefit from being supplemented with additional data. Routinely collected healthcare data provides an alternative information source, offering opportunities for complementing RCTs, including increased strength for more precise estimation of secondary endpoints and subgroup analysis. However, inherent biases (eg, confounding by indication) and the quality and detail of data are a drawback to their use in this context. The recent development of the target trial methodology aims to mitigate some of the biases common to routine data by applying the study design principles of RCTs to non-randomised studies.^10 11^

This protocol defines a strategy to emulate the FIRST-ABC step-up RCT using routinely collected data. This RCT was deemed feasible to emulate using routine data from a high-quality healthcare database, the Paediatric Intensive Care Audit Network (PICANet).^12^ A successful emulation will be defined by comparable estimates with the target trial.^13^

This target trial emulation (TTE) will expand the findings from the FIRST-ABC step-up RCT, offering additional insights from real-world data, and will provide a case study for future work on assessing comparative effectiveness when combining evidence from an RCT and a TTE.^14 15^

### Aim

This study aims to emulate the FIRST-ABC step-up RCT using an observational study design, and benchmark the results against the published trial. We will use advanced quantitative methods to minimise the impact of confounding by indication and allow for heterogeneity according to child characteristics. The analysis will be repeated using a Bayesian approach for follow-up research.

### Objectives

The objectives of the present TTE using PICANet data are:

To describe baseline characteristics and treatment patterns for HFNC and non-invasive ventilatory support (NIV) as a surrogate for CPAP when used as the first-line NRS approach in critically ill children. CPAP is not recorded as a daily intervention in PICANet; however, NIV has been demonstrated to be an appropriate proxy measure for this study.To evaluate the non-inferiority of HFNC, as compared with NIV, on the time to liberation from respiratory support, both overall (primary endpoint) and according to clinically important subgroups.To estimate the effectiveness of HFNC or NIV on mortality at PICU discharge, rate of intubation at 48 hours and duration of PICU stay (secondary endpoints).

## Methods and analysis

### Study design

This is a retrospective cohort study using longitudinal routinely collected data from PICANet.^12^ The study emulates the FIRST-ABC step-up RCT.^16^ The study is planned to start in May 2025 and end in September 2025.

### FIRST-ABC step-up

FIRST-ABC was a master protocol of two pragmatic randomised trials to evaluate the non-inferiority of HFNC versus CPAP for NRS in paediatric critical care.^16^ For the present study, we will focus on the step-up RCT which includes critically ill children requiring NRS for an acute illness. This was powered for the primary endpoint: a sample size of 536 children was required to achieve 90% power with a one-sided type I error rate of 2.5% to exclude the prespecified non-inferiority margin of an adjusted HR of 0.75, and anticipating 5% censoring due to death or transfer. To allow for withdrawal/refusal of deferred consent, the total sample size included 600 children.^17^ Of the 600 children randomised between August 2019 and November 2021, 573 were included in the primary analysis to measure time to liberation from respiratory support using a frequentist approach. This used a modified intention-to-treat (mITT) population, which only included participants who initiated treatment. HFNC met the non-inferiority margin criterion (HR 1.03, 95% CI 0.86 to 1.22). Similar results were seen in the per-protocol analysis (HR 1.03, 95% CI 0.86 to 1.23). Secondary outcomes included mortality at critical care unit discharge (OR 1.22, 95% CI 0.32 to 4.62) and intubation at 48 hours (OR 0.99, 95% CI 0.61 to 1.62). A summary of the components of the FIRST-ABC step-up emulation is reported in table 1.

**Table 1 T1:** Specification of the FIRST-ABC step-up emulation

Protocol component	FIRST-ABC step-up RCT	Target trial emulation
Eligibility criteria	Critically ill children requiring NRS for an acute illness were eligible if meeting the following:	Children included in PICANet between 1 August 2018 and 31 March 2022 and starting HFNC or NIV (as a surrogate for CPAP) will be eligible if meeting the following:
	*Inclusion criteria*	*Inclusion criteria*
	1) Admitted/accepted for admission to PICU/HDU.	1) Admitted to PICU.
	2) Age >36 weeks corrected gestational age and <16 years.	2) Age >36 weeks corrected gestational age and <16 years.
	3) Assessed by the treating clinician to require non-invasive respiratory support for an acute illness.	NA
	*Exclusion criteria*	*Exclusion criteria*
	1) Assessed by the treating clinician to require immediate intubation and invasive ventilation due to severe hypoxia, acidosis and/or respiratory distress, upper airway obstruction, inability to manage airway secretions or recurrent apnoeas.	1) Receiving invasive mechanical ventilation at treatment assignment.
	2) Tracheostomy in place.	2) Tracheostomy in place.
	3) Received HFNC/CPAP for >2 hours in the prior 24 hours.	NA
	4) On home non-invasive ventilation prior to PICU/HDU admission.	NA
	5) Presence of untreated air-leak (pneumothorax/pneumomediastinum).	NA
	6) Midfacial/craniofacial anomalies (unrepaired cleft palate, choanal atresia) or recent craniofacial surgery.	NA
	7) Agreed ‘not for intubation’ or other limitation of critical care treatment plan in place.	NA
	8) Previously recruited to the FIRST-ABC trial.	3) Previously recruited to the FIRST-ABC trial.
	9) Clinician decision to start other form of non-invasive respiratory support (ie, not HFNC or CPAP).	NA
	NA	4) Planned admission.
Treatment strategies	Children were randomised to HFNC or CPAP. Clinicians were permitted to switch from HFNC to CPAP (or vice versa) or escalate to other modes of non-invasive respiratory support or invasive mechanical ventilation if prespecified treatment failure criteria were met.	Children will be assigned to HFNC or NIV as a surrogate for CPAP.
Assignment procedure	Subjects were randomised 1:1 to treatment using a central telephone/web-based randomisation service available 24 hours/7 days per week. The randomisation sequence was computer generated and variable block sizes were used to strengthen allocation concealment. Randomisation was stratified by site and age (<12 months vs ≥12 months).	Participants will be assigned to either strategy they start at baseline. Randomisation will be emulated by adjusting for baseline covariates using advanced statistical methods.
Follow-up period	Starts at randomisation and ends at liberation from respiratory support.	Starts at initiation of HFNC or NIV and ends at liberation from respiratory support.
Outcome	*Primary endpoint*	*Primary endpoint*
	Time to liberation from respiratory support, defined as the start of a 48-hour period during which the child is free of all forms of respiratory support.	Time to liberation from respiratory support, defined as the start of a 2-day period during which the child is free of all forms of respiratory support.
	*Secondary endpoints*	*Secondary endpoints*
	Mortality at critical care (PICU/HDU) unit discharge.	Mortality at PICU discharge.
	Rate of intubation at 48 hours.	Rate of intubation at day 2.
	Duration of critical care (PICU/HDU) stay.	Duration of PICU stay.
	Duration of acute hospital stay.	NA
	Patient comfort.	NA
	Sedation use during NRS.	NA
	Parental stress at 24–48 hours.	NA
Causal contrast	Modified intention-to-treat and per-protocol.	Modified intention-to-treat.
Analysis plan	Analyses of the primary and secondary outcomes were performed according to randomisation group in all consented children who commenced any respiratory support, invasive or non-invasive, following randomisation (primary analysis set) and in all consented children who met the eligibility criteria and commenced the randomised treatment (per-protocol analysis set).	Analyses of the primary and secondary outcomes will be performed according to treatment group in all children who commenced HFNC or NIV, adjusting for all relevant baseline covariates using a doubly robust method.

CPAP, continuous positive airway pressure; FIRST-ABC, FIRST-line support for Assistance in Breathing in Children; HDU, High Dependency Unit; HFNC, high flow nasal cannula; NA, not available; NIV, non-invasive ventilatory support; NRS, non-invasive respiratory support; PICANet, Paediatric Intensive Care Audit Network; PICU, Paediatric Intensive Care Unit; RCT, randomised controlled trial.

### Data source

We will identify the study population using PICANet, an audit database recording details of the treatment of all critically ill children admitted to PICUs across the UK and Ireland.^12^ The PICANet database will be used to identify children eligible for inclusion, providing a representative population of admissions in PICU requiring NRS. The PICANet Admission dataset includes demographic and clinical data on all admissions, daily interventions and information on discharge.^18^

### Study population

The study population will emulate the FIRST-ABC step-up eligibility criteria within the constraints of the available routinely collected data and will include children admitted to PICU between 1 August 2018 and 31 March 2022, aged >36 weeks corrected gestational age and <16 years, and starting HFNC or NIV as a surrogate for CPAP within 2 days from PICU admission. Children will be excluded if any of the following criteria are recorded: intubation and/or invasive ventilation, tracheostomy, previously recruited in FIRST-ABC, planned admission.^16^

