### Exposures

In FIRST-ABC step-up, children randomised to HFNC were started at a flow rate based on body weight. When a child was deemed ready for weaning, the flow rate was reduced by 50%. Children randomised to CPAP were started at a pressure of 7–8 cm H_2_O. When a child was deemed ready for weaning, the pressure was reduced to 5 cm H_2_O. Both HFNC and CPAP were delivered through devices and interfaces already used as part of routine care at sites. For both groups, the fraction of inspired oxygen (FiO_2_) was titrated to maintain peripheral oxygen saturation (SpO_2_) of 92% or higher. Clinicians were permitted to switch from HFNC to CPAP (or vice versa) or escalate to other modes of NRS or invasive mechanical ventilation if prespecified treatment failure criteria were met (FiO_2_ ≥0.60, severe respiratory distress, patient discomfort).

In this study, exposure groups will include children who started HFNC or NIV, as per daily interventions in the PICANet Admission Data Collection Form.^12^ CPAP is not recorded in the PICANet daily procedures and, therefore, it cannot be identified. As NIV cannot be used to record HFNC, we will use NIV as a surrogate for CPAP, providing treatment strategies for the TTE.^18^

The assumption that NIV could approximate CPAP was tested on the FIRST-ABC step-up population linked to the relevant PICANet sample using a previously reported strategy.^19^ Of the children with a recorded activity date that matched the randomisation date, or the following date, 86% of children with recorded NIV were assigned to CPAP in FIRST-ABC step-up and 86% of children with recorded HFNC were assigned to the same treatment in FIRST-ABC step-up.

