### Outcomes

The following outcomes will be measured:

Primary endpoint:

Time to liberation from respiratory support, defined as the start of a 2-day period free of all forms of respiratory support. Children discharged from PICU will be assumed to be liberated from all forms of support.

Secondary endpoints:

Mortality at PICU discharge.Rate of intubation at day 2.Duration of PICU stay.

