### Sample size considerations

In the design of the FIRST-ABC step-up RCT, it was anticipated that 508 observed events would achieve 90% power with a one-sided type I error rate of 2.5% to exclude the prespecified non-inferiority margin of an HR of 0.75. To account for censoring from death or transfer and refusal or withdrawal of consent, the target sample size was set at 600 children.^5^

The design of the TTE recognises that between 2019 and 2022 there were 14 875 respiratory admissions in PICANet.^21^ From a previous PICANet sample of 2 years, it was anticipated that more than 3000 children (of which 2/3 assigned to HFNC) would meet the pre-defined eligibility criteria and start the study treatments in the first 2 days of critical care admission. The primary outcome will be tested for non-inferiority using the RCT margin (corresponding to approximately a 16-hour increase in median time to liberation), and the secondary outcomes for superiority. Among the secondary outcomes, the rate of intubation at 48 hours was considered of high importance by patient representatives. With a proportion of 15.4% from FIRST-ABC step-up results, we anticipate that, with unequal group sizes, a two-sided type I error rate of 5%, and 90% power, the study will be able to detect a 4% absolute difference in proportions.^22^

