## Strengths and limitations

This TTE will benefit from the large available sample size provided by the PICANet database, as well as its representative coverage of the FIRST-ABC step-up target population.

FIRST-ABC step-up will be emulated within the constraints of routinely collected data. As in any observational study, confounding and selection bias are major concerns. We will mitigate these risks through the TTE design and a validated and rich covariate data set, which will enable the key trial eligibility criteria to be applied, and most potential confounders to be included in the adjustment.

The inclusion of healthier children compared with FIRST-ABC step-up could dilute the effect towards the null, while failing to exclude children who initiated treatment before PICU admission could artificially shorten the follow-up period, further biasing the effect towards the null. In both cases, the bias is assumed to be non-differential. Other non-replicable exclusion criteria are contraindications to the treatments, and their unavailability in PICANet is mitigated by the treatment initiator design.

Study treatments and endpoints replication is constrained by the limits imposed by routinely collected data, but preliminary checks have proved NIV to be a valid alternative to CPAP.

Because the primary outcome cannot be assessed beyond PICU discharge, we will assume that respiratory support ends at the time of PICU discharge. This assumption may introduce differential bias as HFNC is more likely than CPAP to be continued on the ward.^49^

The use of daily rather than hourly data may limit our ability to target a population fully comparable to that in FIRST-ABC and may hinder accurate identification of the treatment received. Strategies will be implemented to minimise potential differences between treatment groups.

Additionally, DR analysis methods will be implemented, and sensitivity analyses will be performed to assess the robustness of the findings. Missing data are expected to be minimal.

This study will be reported using the Strengthening the Reporting of Observational Studies in Epidemiology guidelines.^50^

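### The invasive-ventilation exclusion is worded in two incompatible ways, and neither wording settles how a child who starts HFNC/NIV and is intubated on the same calendar day is classified

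*Protocol article*

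**What the plan says.** All references are to the Protocol article.

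- **Table 1, exclusion criteria, emulation column:** "Receiving invasive mechanical ventilation at treatment assignment".
- **Study population:** "Children will be excluded if any of the following criteria are recorded: intubation and/or invasive ventilation", followed by tracheostomy, earlier recruitment to the trial and planned admission. It does not say when the intubation or ventilation must have been recorded. The same section admits children "starting HFNC or NIV as a surrogate for CPAP within 2 days from PICU admission".
- **Exposures:** "exposure groups will include children who started HFNC or NIV, as per daily interventions in the PICANet Admission Data Collection Form".
- **Strengths and limitations:** "The use of daily rather than hourly data may limit our ability to target a population fully comparable to that in FIRST-ABC". It adds that the treatment received may be hard to identify accurately.
- **Outcomes:** one secondary endpoint is "Rate of intubation at day 2". Under Sample size considerations, "the rate of intubation at 48 hours was considered of high importance by patient representatives", and a detectable difference of 4 percentage points is given from a 15.4% proportion, at two-sided 5% and 90% power, with more than 3000 children, two thirds of them on HFNC.
- **Planned analyses (frequentist):** each child is analysed in the group first started, whatever treatment follows.

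**The concern.** The two exclusion statements differ in timing and in scope, and they decide who enters the study. An untimed rule based on any recorded intubation cannot stand beside an intubation endpoint, or beside an analysis that keeps children in their starting group whatever happens next.

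The second difficulty remains after the wording is aligned. With day-level records, ventilation before the start of HFNC/NIV and ventilation after it has failed look the same when they share a date. If every such child is dropped, cohort entry depends on an event that may have happened after baseline. The trial excluded children judged to need immediate intubation and then followed the rest from randomisation, so it counted early failures.

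At stake is the secondary endpoint that patient representatives singled out. The primary endpoint may also be affected, because children intubated on the first day are plausibly slow to be liberated from support. Success is defined in the Introduction as estimates comparable with the trial's, so a distortion that differs by arm could be misread as a failed or a successful emulation.

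**Working it through.** **1. The two rules side by side.**

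| Child | Table 1 | Study population, as written |
|---|---|---|
| Starts HFNC/NIV, intubated on a later day | in | out |
| Ventilated, extubated, then starts HFNC/NIV | in | out |
| Starts HFNC/NIV, intubated later the same day | in if the order is known; out if applied by calendar day | out |

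The first row is the direct conflict with the day-2 intubation endpoint and with the analysis by starting group.

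**2. What in the plan could recover same-day cases.** The immortal-time sensitivity analysis drops children assigned on the day after admission. Those who start on the admission day remain, and the same-day order is just as unresolved for them. Doubly robust adjustment balances measured baseline covariates among children in the cohort; it does not bring back excluded events. The Covariates section lists mechanical ventilation among items collected at PICU admission. This could help to order some records, but the article does not state its exact timing.

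**3. The plan's own figure.** For smaller-arm size n₁, allocation ratio r = 2 and difference d (pooled variance under the null):

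n₁ = [1.960·√(p̄(1−p̄)(1+1/r)) + 1.282·√(p₁(1−p₁) + p₂(1−p₂)/r)]² / d²

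- 15.4% (NIV) vs 11.4% (HFNC): n₁ = 1131, total 3393.
- 15.4% (NIV) vs 19.4% (HFNC): n₁ = 1423, total 4269.

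At exactly 3000 (1000 vs 2000), power for 4 points is 86% and 77% respectively. The plan says more than 3000, based on a 2-year sample, and the study window is 44 months. Scaling gives 3000 × 44/24 = 5500 (an assumption), with power of 98% and 96%. The 4-point figure is therefore not called wrong.

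**4. Effect of removing start-day intubations.** Let f be the share of 48-hour intubations recorded on the start day and removed. The documents give no value for f, so the values below are assumptions.

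Observed rate = p(1−f)/(1−pf)

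- f = 25%: 0.154 × 0.75 / (1 − 0.0385) = 0.1155/0.9615 = 12.0%.
- f = 50%: 0.154 × 0.50 / (1 − 0.077) = 0.077/0.923 = 8.3%.

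Of 0.154 × 3000 = 462 intubations, about 116 and 231 are lost.

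**5. Equal f in both arms.** The residual odds are [p(1−f)/(1−pf)] / [(1−p)/(1−pf)] = p(1−f)/(1−p). The factor (1−f) cancels between arms, so the crude odds ratio does not change. The risk difference and power do. In each cell, the first figure is for HFNC higher (19.4%) and the second for HFNC lower (11.4%), against 15.4% on NIV.

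| f | Size of difference, points | Power, N = 3000 | Power, N = 5500 |
|---|---|---|---|
| 0 | 4.0 / 4.0 | 77% / 86% | 96% / 98% |
| 25% | 3.3 / 3.2 | 67% / 77% | 90% / 95% |
| 50% | 2.4 / 2.3 | 51% / 62% | 77% / 86% |

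**6. Unequal f.** With no true difference, the odds ratio (HFNC vs NIV) is (1−f_HFNC)/(1−f_NIV).

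- f = 25% on HFNC and 50% on NIV: 12.0% vs 8.3%, OR = 0.75/0.50 = 1.50.
- Reversed: OR = 0.50/0.75 = 0.67.

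The trial's own estimate for intubation at 48 hours was an OR of 0.99 (95% CI 0.61 to 1.62).

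**The case against.** The strongest reply is that the Study population sentence is shorthand. It summarises entry conditions, the other items in its list are baseline conditions, and Table 1 supplies the time point. The intubation endpoint and the analysis by starting group show that the authors do not intend to delete later intubations. That is probably right. A reader might infer that the intubation endpoint is zero by construction; the literal sentence gives that result, but the document as a whole does not support it as the plan.

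A reader might also infer that both wordings condition entry on a post-baseline event. Table 1's wording does not. The problem arises only if it is applied by calendar day. The article does not say that it will be, although daily records are the only resolution it describes. A rule for same-day records may sit in a fuller protocol or SAP.

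Finally, the limits of daily data are disclosed in general terms, and equal removal in both arms leaves the odds ratio, the scale on which the trial result is quoted, unchanged. Both points stand. But the disclosure does not mention lost intubation events, and nothing in the documents shows that the share would be equal between arms. None of this removes the conflict between two printed eligibility rules.

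**Conclusion.** The point holds in two parts. First, the two eligibility statements are incompatible and must be reconciled; this needs no assumption. Second, aligning them with Table 1 leaves same-day cases open, and a calendar-day reading would drop children intubated after starting treatment.

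The size of the second part cannot be computed from the documents. The 12.0% to 8.3% range rests on an assumed 25% to 50% start-day share, and the odds ratios of 1.50 and 0.67 rest on an assumed imbalance of 25% against 50%. The direction of any bias is unknown. The effect on time to liberation is plausible but not quantified.

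A reader might conclude that the study loses its power for intubation or can no longer be compared with the trial. The documents support neither. Power depends on a cohort size stated only as more than 3000, and the odds ratio is distorted only if the removed share differs by arm.

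**What to change.** 1. Use one time-anchored criterion in both Table 1 and Study population: exclude children with invasive ventilation recorded before the first HFNC/NIV day. This also excludes a child ventilated on an earlier day and extubated before starting, whom Table 1 as worded would keep, so that choice should be stated openly.
2. Prespecify how same-day records are classified, using the admission mechanical ventilation item once its timing has been checked.
3. State that intubations after the start of HFNC/NIV count as outcomes.
4. Run the intubation and primary analyses under both extremes, with all same-day cases kept and with all excluded, and report the number of same-day cases by arm. This bounds the uncertainty about order.

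Which classification is primary is a judgement between two misclassifications. The inclusive rule may keep some children ventilated before HFNC/NIV on the same day and count that intubation as an outcome; the exclusive rule discards genuine early failures. The cost is a wording change and one extra sensitivity run.
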